#### Randomised controlled trial (Objective 2)

Analysis of the randomised comparison between MRI/US fusion-guided biopsy and standard TRUS-guided biopsy will be implemented according to the ICH E9 “Statistical Principles in Clinical Trials”. Analysis will be based on the intention-to-treat principle. The key outcome for the randomised study is to measure whether the MRI/US fusion-guided biopsy can improve the detection of cancer foci and to establish the reliability of the pre-biopsy MRI for the localisation of cancer foci within the prostate gland.

Secondary outcomes will include the following:
PCa detected on fusion biopsy which is missed on TRUS biopsySafety outcomes of death, and side effects such as pain and bleeding with the severity and duration of symptoms recorded in each randomised groupComparison of MRI-negative standard of care TRUS-guided biopsies with MRI-positive TRUS histopathology to facilitate analysis of the diagnostic accuracy of MRI in men suspected of a target condition

Binary outcomes such as cancer (Yes/No) and pain (Yes/No) will be analysed using logistic regression with the intervention arm as a binary variable in the model. All analyses will be stratified by site and minimisation variables, and adjusted for prostatic volume and maximum lesion size. Outcomes such as the Gleason Score (GS) and the number of lesions (depending on the range of values obtained) will be analysed as continuous linear regression or ordinal logistic regression. Subgroup analyses will be carried out as secondary analyses by adding treatment by subgroup variable interaction terms in the regression model. Analyses will be conducted by the study statisticians utilising SAS (9.4).

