## Background

### Introduction and rationale

Men suspected of having prostate cancer (PCa) because of high levels of serum prostate-specific antigen (PSA) and/or abnormal digital rectal examination (DRE) are offered prostate biopsies guided by transrectal ultrasound (TRUS). Several challenges are seen in this crucial step. Firstly, the incidence of false-negative biopsies (i.e. clinically significant tumours not being detected) may be as high as 35% in first-time biopsies [1]; secondly, up to 44% of men younger than 70 years of age may need a second set of biopsies following initial negative results [2]; thirdly, up to 50% of PCa cases currently detected by these methods may not be clinically relevant when considering other patient-related factors; fourthly, data from UK Prostate Testing for Cancer and Treatment (ProtecT) has shown significant morbidity of the biopsy procedure, at times even leading to patient death [3]; and, finally, several studies have shown no improvement in PCa mortality, despite increased detection rates through screening programmes [4], and the number of deaths from PCa in the UK sadly remains largely unchanged.

Post-biopsy standard of care magnetic resonance imaging (MRI) is offered to patients with positive biopsy results or when there is a continuous increase in PSA levels despite negative biopsies. The performance of post-biopsy MRI in the staging and detection of PCa is significantly degraded by post-biopsy artefact [5, 6]. Therefore, it is recommended that MRI should be performed at least 10 weeks after biopsy, and if possible after 20 weeks [7]. Such a wait is unacceptable to patients and causes breaching of time with respect to treatment guidelines. Improving early detection of clinically significant PCa would very likely save many lives by refining the stratification of patients for optimising the treatment of significant disease, whilst simultaneously diminishing patient anxiety and morbidity through overdiagnosis and overtreatment.

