### Objectives

The primary objective is to determine whether using multiparametric MRI (mpMRI) can improve cancer detection and the characterisation of PCa, and primary outcome measurements include:
Number of PCa cases detected by mpMRI when compared to gold-standard prostatectomy specimensNumber of clinically significant cancers detected by mpMRI when compared to gold-standard prostatectomy specimens

The secondary objective is to assess whether MRI/US fusion-guided biopsy can reduce the number of false-negative biopsies, and key outcome measurements include:
Number of cancers detected in each randomised group, namely the intervention group (TRUS and MRI/US fusion-guided biopsy) vs. the standard of care group (TRUS only biopsy)Number of clinically significant cancers detected in each randomised group

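### The Objectives and the analysis section name different key outcomes for the randomised comparison, and the analysis section's outcome (cancer foci) does not measure missed clinically significant cancer

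*Protocol article*

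**What the plan says.** All places are in the protocol article.

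- **Introduction and rationale** explains the term false-negative: "the incidence of false-negative biopsies (i.e. clinically significant tumours not being detected) may be as high as 35% in first-time biopsies". It also says that up to half of the cancers now detected may not be clinically relevant, and gives less overdiagnosis and overtreatment as part of the rationale.
- **Objectives** sets the aim of the randomised part: "The secondary objective is to assess whether MRI/US fusion-guided biopsy can reduce the number of false-negative biopsies". Two key outcomes follow: "Number of cancers detected in each randomised group, namely the intervention group" versus standard care, and "Number of clinically significant cancers detected in each randomised group".
- **Randomised controlled trial (Objective 2)**, the analysis section, states: "The key outcome for the randomised study is to measure whether the MRI/US fusion-guided biopsy can improve the detection of cancer foci". The same sentence adds the reliability of pre-biopsy MRI for locating foci. On modelling it says: "Binary outcomes such as cancer (Yes/No) and pain (Yes/No) will be analysed using logistic regression". Gleason score and number of lesions are to be analysed by linear or ordinal regression. The section does not mention clinically significant cancer.
- **Allocations and interventions** gives one arm TRUS biopsy plus fusion biopsy at the same attendance, and the other arm TRUS biopsy only. The article gives no core numbers.

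**The concern.** One randomised comparison has two differently stated key outcomes. They differ in unit (foci within a gland against cancers per arm) and in whether clinical significance counts. The analysis section's version also holds two questions in one, because MRI localisation is a question of accuracy and not a contrast between arms.

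The choice matters because the sampling is unequal. The intervention arm has everything the control arm has, plus fusion cores. It can be expected to find at least as many foci and at least as many low-risk cancers. If the analysis section is taken as the governing text, the trial could report better detection on its key outcome without having found more men with clinically significant cancer. Extra insignificant cancer would count towards success, although the rationale seeks to reduce overdiagnosis.

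**Working it through.** **1. The plan's own figure.** Study population and setting expects 600 men scanned, 80% of them MRI-positive, randomised 1:1: 600 × 0.80 / 2 = 240 per arm. This reproduces. It is a feasibility count. The article states no event rate, effect size or power for the randomised comparison, and its one power statement concerns Objective 1. The calculations below are therefore illustrations at 240 per arm with an assumed two-sided 5% level.

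**2. The passages side by side.**

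| | Objectives | Analysis section |
|---|---|---|
| Key outcome | cancers and clinically significant cancers | cancer foci, with MRI localisation |
| Unit | number per arm | lesion |
| Clinical significance | one of the two outcomes | not mentioned |
| Contrast between arms | yes, both | foci yes, localisation no |

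Only the clinically significant count in the Objectives matches the Introduction's meaning of a false-negative biopsy.

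**3. A gain confined to insignificant cancer.** Assume that the rate of significant cancer is equal in both arms and that all extra detection is insignificant disease. With control rate p0, intervention rate p1 and mean m:

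power = Φ[(p1 − p0 − 1.96·s0) / s1], where s0 = √(2m(1−m)/240) and s1 = √((p0(1−p0) + p1(1−p1))/240).

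For 50% against 60%: s0 = 0.0454, s1 = 0.0452, and Φ[(0.10 − 1.96 × 0.0454)/0.0452] = Φ(0.24) = 0.60.

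| Any cancer, control → intervention (assumed) | Chance of p < 0.05 | True gain in significant cancer |
|---|---|---|
| 50% → 58% | 0.42 | 0 |
| 50% → 60% | 0.60 | 0 |
| 50% → 63% | 0.82 | 0 |

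**4. Extra cores with no targeting benefit.** Take TRUS sensitivity as 65%, from the Introduction's miss rate of up to 35%. Assume 10 to 12 standard cores, 2 to 6 extra cores, and 50% to 70% of men with cancer. With independent cores, 12 standard and 4 extra, sensitivity becomes 1 − 0.35^(16/12) = 0.753. The chance of a significant arm difference is then 0.22 when 50% of men have cancer and 0.35 when 70% do. Over the whole grid, including models in which cores from one man are correlated, sensitivity rises to about 67% to 81% and that chance runs from about 5% to 71%. Since 35% is the miss rate for clinically significant tumours, the same arithmetic applies to significant cancer.

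**5. What the significant-cancer outcome can detect.** Solving the formula in step 3 for 80% power at 240 per arm:

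| Control rate (assumed) | Absolute gain needed |
|---|---|
| 20% | 11.1 points |
| 30% | 12.3 points |
| 40% | 12.7 points |
| 50% | 12.7 points |

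**The case against.** The best defence is to read the article as a whole. The Objectives already plan a count of clinically significant cancers by arm. As a Yes/No outcome per man, that count fits the analysis section's open class of binary outcomes. Gleason score is analysed as well. The fuller protocol and the analysis plan, which are not shown, may assign a model to each outcome. The Objectives also list any cancer as a key outcome, so detection of any cancer is a declared aim, and the gloss on false-negative biopsies comes from a background sentence.

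Much of this stands, and it rules out four stronger readings that a reader might draw:

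- *Any cancer (Yes/No) is the declared key outcome.* It is not. It appears with pain as an example for the choice of model.
- *Significant cancer is not compared, so the trial's question goes unanswered.* The count by arm is pre-specified in the Objectives and would be reported. It is missing only from the analysis section.
- *The intervention arm wins by construction.* Core numbers are not given, and step 4 shows that extra sampling can produce a positive result but need not.
- *Changing the endpoint removes the extra-sampling effect.* It does not, because additional cores also raise detection of significant cancer.

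The defence does not remove the conflict. Two sections each say what the key outcome is, and they disagree. Choosing a model later does not settle which outcome carries the conclusion. Gleason score on a continuous or ordinal scale is also not the proportion of randomised men with significant cancer.

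**Conclusion.** The point holds as an inconsistency between the Objectives and the analysis section that should be corrected. The analysis section's key outcome differs from the Objectives in unit and in clinical significance, includes a component that is not an arm comparison, and does not measure the objective as the Introduction explains it. A positive result on foci would not by itself show fewer missed significant cancers.

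This conclusion rests on the text alone. The 42%, 60% and 82% figures depend on assumed detection rates and on the assumption that all of the gain is insignificant disease, for which the documents give no source. They show what could happen and do not predict it. The range of about 5% to 71% likewise rests on assumed core numbers, cancer prevalence and correlation between cores.

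**What to change.** In the analysis section for Objective 2:

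1. Name one key outcome per man: at least one clinically significant cancer on biopsy (Yes/No), compared by allocated arm, using the trial's own definition of clinically significant.
2. Keep any cancer (also listed in the Objectives), clinically insignificant cancer and number of foci as supporting outcomes, and mark the same order in the Objectives.
3. Move MRI localisation reliability to Objective 1.
4. State that a positive result will be read as the effect of adding fusion cores to the standard biopsy. The new outcome deals with overdiagnosis but not with the extra sampling.

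The change is one of wording, since the Objectives already plan to count significant cancers by arm. As a protocol change it needs approval from the Sponsor, REC and NHS R&D. With 416 of 600 men recruited at publication, it should be made before outcomes by arm are seen. The statistical cost is that clinically significant cancer is less frequent than any cancer, so the expected effect may be less favourable against the detectable gains of about 11 to 13 points shown in the working.

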### Allocations and interventions

All enrolled participants will be offered 1.5 Tesla or 3.0 Tesla mpMRI prior to prostate biopsy where this is not already within the standard care pathway. A subgroup of participants with positive pre-biopsy MRI will be randomised into two further subgroups at a 1:1 ratio. Randomisation will be via TRUST, a web-based, good clinical practice (GCP)-compliant randomisation system run by the Health Informatics Centre (HIC). Randomisation will be implemented with random block sizes stratified by site and minimised by: the Prostate Imaging Reporting and Data System (PI-RADS) suspicion score (3–5); index lesion size (in two categories: above and below 6 mm in maximal diameter on MRI); age (40–59 years, 60–75 years); and PSA < 10.1 or PSA ≥ 10.1 to ≤ 20 ng/ml). The first subgroup will undergo a TRUS and MRI/US fusion-guided biopsy and the second will undergo standard of care TRUS-guide biopsies only. The MRI/US fusion-guided biopsy will be performed during the same attendance as the TRUS-guided biopsy***.*** TRUS and MRI/US fusion-guided biopsies will be performed by NHS-accredited radiologists and/or urologists from the research team. The persons undertaking the biopsy will have prior experience and will have received appropriate training from clinical experts and/or the equipment supplier’s application specialist(s). Those participants with negative pre-biopsy MRI will follow the local standard of care pathway; where this includes biopsy, data from the biopsy will be collected for analysis.

In a subgroup of patients who undergo radical prostatectomy, the prostatectomy specimen will be sectioned using customised moulds [9, 10] allowing for direct comparison with mpMRI. This will be carried out in NHS Tayside, NHS Grampian and other sites where local facilities allow. Comparison of mpMRI with a reference standard of radical prostatectomy pathology will be performed as the primary outcome.

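### The randomised comparison adjusts for age and PSA only in two bands and omits prior biopsy: a small, avoidable loss of efficiency

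*Protocol article*

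**What the plan says.** The section on the randomised controlled trial (Objective 2) states that binary outcomes such as cancer "will be analysed using logistic regression with the intervention arm as a binary variable in the model". It then fixes the adjustment set, under which every analysis is "stratified by site and minimisation variables, and adjusted for prostatic volume and maximum lesion size".

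The section on allocations and interventions defines the minimisation variables:

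- PI-RADS suspicion score, 3 to 5
- "index lesion size (in two categories: above and below 6 mm in maximal diameter on MRI")
- "age (40–59 years, 60–75 years")
- "PSA < 10.1 or PSA ≥ 10.1 to ≤ 20 ng/ml"

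The inclusion criteria admit men aged 40 to 75 with PSA up to 20 ng/ml. The exclusion criteria rule out a prostate biopsy only if it fell within the last 12 months, and they exclude men with a history of prostate cancer. A man with an older biopsy that did not diagnose cancer can therefore be randomised. Prior biopsy is not among the minimisation variables or the listed covariates.

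**The concern.** An analysis stratified by the minimisation variables uses them as they were defined, so age and PSA each enter with two levels. A man of 60 and a man of 75 are treated alike, as are PSA values of 2 and 10. Lesion size is handled differently: it is also a two-level minimisation factor, but the analysis adds maximum lesion size as a further term. Age and PSA get no such term, although their values are needed to apply the eligibility limits and the minimisation bands.

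Prior biopsy is the second omission. The introduction gives its false-negative figure of up to 35% for first-time biopsies and adds that "up to 44% of men younger than 70 years of age may need a second set of biopsies following initial negative results". The randomised objective is to reduce false-negative biopsies, so biopsy history is a plausible predictor of the outcome.

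In a logistic model, leaving out a prognostic covariate costs some power for the arm effect and pulls the estimated odds ratio towards 1. What is at stake is precision in the comparison of cancer detection between arms.

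**Working it through.** **The plan's own figure.** The article expects 80% of about 600 MRI scans to show a suspicious lesion, and those men "will be randomised into two further subgroups at a 1:1 ratio". So 600 × 0.80 / 2 = 240 per arm, or 480 in total, which matches the article. It states no significance level, effect size or power for the randomised comparison, so there is no power figure to reproduce.

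**Method.** Logistic regression was simulated with 480 men allocated 1:1, 1,500 replicates per scenario. Three models were fitted to the same data: (1) two-level age and PSA; (2) continuous age and log PSA instead; (3) model 2 plus prior biopsy. All covariate effects are assumptions.

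**Set A.** Log odds of 0.3 to 0.5 per SD of age and of log PSA; prior-biopsy log odds ratio −0.8 to −1.0, present in 15 to 25% of men.

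| Scenario | Model 1 | Model 2 | Model 3 | Gain 1→2 | Gain 1→3 |
|---|---|---|---|---|---|
| A1 | 84.9% | 86.2% | 86.7% | 1.3 | 1.8 |
| A2 | 80.2% | 81.8% | 83.5% | 1.6 | 3.3 |
| A3 | 85.1% | 85.1% | 85.6% | 0.0 | 0.5 |

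**Set B.** Conditional log odds ratio for arm 0.55. All three models also contained prostatic volume, lesion size and PI-RADS score. Weak / moderate / strong scenarios used log odds of 0.2 / 0.4 / 0.6 per SD of age and of log PSA, and prior-biopsy log odds ratios of −0.4 / −0.8 / −1.2 with prevalence 15% / 20% / 30%.

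| Scenario | Model 1 | Model 2 | Model 3 | Gain 1→2 | Gain 1→3 |
|---|---|---|---|---|---|
| Weak | 76.1% | 76.7% | 77.3% | 0.6 | 1.2 |
| Moderate | 75.3% | 75.5% | 76.4% | 0.2 | 1.1 |
| Strong | 69.7% | 71.9% | 74.7% | 2.2 | 5.0 |

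The Monte Carlo standard error of one power figure is about √(0.75 × 0.25 / 1,500) = 1.1 points. Differences between models are steadier than that, because the models share data, but the smallest gains should not be read closely.

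**Estimate and test (set B).** The mean estimated log odds ratio across models 1, 2 and 3 was 0.550, 0.555, 0.559 (weak); 0.530, 0.545, 0.558 (moderate); and 0.501, 0.530, 0.565 (strong). With no arm effect, rejection rates were 5.6%, 5.6%, 5.5%; 5.1%, 5.3%, 5.2%; and 4.9%, 4.8%, 4.3%. The Monte Carlo standard error here is √(0.05 × 0.95 / 1,500) = 0.6 points, so all are compatible with 5%.

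**Limits.** Site and the 6 mm lesion category were not in the set B models, and allocation was simple 1:1 rather than minimised. Models 2 and 3 replaced the age and PSA bands, whereas the fix below keeps them. That variant was not simulated; its extra cost is two nuisance parameters among 480 men.

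**The case against.** The strongest reply is that the adjustment set is already sound. Adjusting for the factors used in the allocation is correct practice, and the article adds prostatic volume and lesion size. The coding of covariates and the choice of one more are matters a condensed article may leave to the analysis plan, and the article does not say outright how age and PSA are coded. The two-level reading is an inference from the bands in the allocation section. It is the natural one, since stratifying by a variable requires categories, but if the analysis plan already uses continuous terms, that part of the point falls away. Otherwise the article names a specific adjustment set, and improving it is a concrete change to a stated model.

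Four stronger readings are tempting, and the documents do not support them.

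- *Prior-biopsy status is already held.* A reader might infer this from the eligibility check. That check needs only whether a biopsy took place in the last 12 months, and nowhere does the article say that older history is recorded.
- *The introduction shows that prior biopsy is prognostic here.* It gives no detection rate by biopsy history, and none for MRI-positive men, who are the ones randomised.
- *Chance imbalance in prior biopsy distorts the result.* With an assumed 25% prevalence and detection of 55% against 30%, the SD of the imbalance is √(0.25 × 0.75 × 2 / 240) = 4.0 points. Multiplied by the 0.25 gap this is 1.0 point, or about ±2 points at 95%. That is ordinary sampling variation, already in the standard error.
- *The smaller odds ratio under the coarser model is bias.* The odds ratio changes with the covariates conditioned on, so the coarser model estimates a less conditional quantity. Its test remains valid.

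The reply is also right that the gain is small: only the strong scenario of set B reaches 5 points.

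**Conclusion.** The point holds as an optional, low-cost improvement. As written, the model uses age and PSA in two levels only and leaves prior biopsy out. Across the six scenarios, continuous age and log PSA gain about 0 to 2 points of power, and the total with prior biopsy is about 0.5 to 5 points. Type I error is unaffected.

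These sizes depend on assumed covariate effects, an assumed arm effect and an assumed share of previously biopsied men, none of which the article gives. The case is firmer for age and PSA, whose values the trial must hold. For prior biopsy it is conditional on the history being available.

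**What to change.** In the logistic models for cancer and for clinically significant cancer:

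1. Keep site, the minimisation factors, prostatic volume and maximum lesion size as stated.
2. Add age and log PSA as continuous covariates alongside their bands. Any collinearity with the bands affects those coefficients, not the arm effect.
3. Establish whether biopsy history beyond 12 months is recorded or can be taken from clinical records. If so, add prior biopsy (none or any) as a covariate.
4. Write this into the analysis plan before outcome data are analysed, so that covariate choice cannot look data-driven. The article reports 416 men recruited, with recruitment continuing to 30 June 2020.

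The cost is up to three extra parameters (age, log PSA, prior biopsy) in a model of about 480 men, plus retrieval of biopsy history if it is not already captured. Eligibility, allocation and procedures do not change.

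### The randomised comparison of Gleason Score allows a linear regression that only men with detected cancer can enter, so it would compare subsets selected by the outcome the intervention is meant to change

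*Protocol article*

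**What the plan says.** All references are to the protocol article.

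- **Randomised controlled trial (Objective 2)**, analysis principle: "Analysis will be based on the intention-to-treat principle".
- Same section, presence of cancer: "Binary outcomes such as cancer (Yes/No) and pain (Yes/No) will be analysed using logistic regression with the intervention arm as a binary variable". Men without cancer are thus expected in both arms.
- Same section, grade: "Outcomes such as the Gleason Score (GS) and the number of lesions (depending on the range of values obtained) will be analysed as". The two options that the sentence goes on to name are "continuous linear regression or ordinal logistic regression". No value, category or analysis set is given for a man whose biopsy shows no cancer.
- Same section, the key outcome is to "measure whether the MRI/US fusion-guided biopsy can improve the detection of cancer foci". **Objectives** states the secondary objective as to "assess whether MRI/US fusion-guided biopsy can reduce the number of false-negative biopsies".
- **Allocations and interventions**: "The MRI/US fusion-guided biopsy will be performed during the same attendance as the TRUS-guided biopsy". The intervention arm has TRUS plus fusion biopsy; the control arm has TRUS alone.
- **Objectives** also lists, as a key outcome: "Number of clinically significant cancers detected in each randomised group".

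**The concern.** Gleason Score grades cancer that has been found. A linear model for it has no place for a benign biopsy unless someone invents a number, so in practice it is fitted to cancer-positive men only. Whether a man is cancer-positive is settled after randomisation, by the biopsy strategy itself. If fusion biopsy adds detections, the intervention arm's cancer-positive set contains men whose counterparts in the control arm are recorded as benign and drop out. The arm coefficient then mixes two things: any change in the grade assigned to men who would be positive either way, and the grade of the additional men who enter. Randomisation does not protect that contrast.

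At stake is a published difference in Gleason Score, with a p-value, that could be read as evidence on finding aggressive disease. If the extra cancers are mostly low grade, fusion looks worse on this measure while finding more higher-grade cancer; if they are mostly high grade, the cancer-only difference favours fusion.

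**Working it through.** **1. The plan's own figure.** From Study population and setting: 1000 − 350 − 50 = 600 men scanned; 0.80 × 600 = 480 with a suspicious lesion; 480 / 2 = 240 per arm. This reproduces. The article gives no detection rate or grade distribution for the randomised arms, so everything below rests on assumed rates.

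**2. Formula.** Let p be the proportion positive on TRUS, e the extra proportion detected when fusion is added, m₀ the mean score of TRUS-detectable cancers (the same in both arms) and mₑ the mean score of the extra cancers. The cancer-only difference in means is then

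e / (p + e) × (mₑ − m₀).

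It is zero only if e = 0 or the extra cancers have the same mean grade.

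**3. Assumed inputs.**
- p = 40% or 50%; e = 5, 10 or 15 percentage points.
- TRUS-detectable cancers: scores 6/7/8/9 in 35/45/10/10%, so m₀ = 2.10 + 3.15 + 0.80 + 0.90 = 6.95.
- Extra cancers mostly low grade: 6/7 in 80/20%, mₑ = 6.20.
- Extra cancers mostly high grade: 7/8/9 in 65/20/15%, mₑ = 7.50.

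The rejection rates come from 4,000 simulated trials per setting with 240 men per arm, using an unadjusted two-sample t-test at two-sided 0.05.

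| p | e | Men with a score, TRUS vs fusion arm | Low-grade extras: difference (p<0.05) | High-grade extras: difference (p<0.05) |
|---|---|---|---|---|
| 40% | 5 | 96 vs 108 | −0.08 (9.8%) | +0.06 (8.2%) |
| 40% | 10 | 96 vs 120 | −0.15 (22.7%) | +0.11 (14.3%) |
| 40% | 15 | 96 vs 132 | −0.20 (39.5%) | +0.15 (23.4%) |
| 50% | 5 | 120 vs 132 | −0.07 (8.4%) | +0.05 (7.4%) |
| 50% | 10 | 120 vs 144 | −0.125 (20.0%) | +0.09 (13.4%) |
| 50% | 15 | 120 vs 156 | −0.17 (35.7%) | +0.13 (21.2%) |

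When the extra cancers have the same grade mix, the difference is 0 and rejection stays between 4.5% and 5.3%.

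**4. Sign reversal, one row in full** (p = 40%, e = 10 points, low-grade extras).
- Score 6 among cancers in the fusion arm: (0.40 × 0.35 + 0.10 × 0.80) / 0.50 = 0.44.
- Score 7 or more among cancers: 65% (TRUS) vs 56% (fusion).
- Score 7 or more among all randomised: 0.40 × 0.65 = 26% vs 0.50 × 0.56 = 28%.

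The cancer-only comparison falls while the all-randomised comparison rises.

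**5. Would one proportional-odds estimate on all men settle it?** Take a second assumed example. TRUS arm: benign 45%, scores 6/7/8 in 20/20/15%. Fusion arm: 35%, then 27/22/16%. The cumulative odds ratios are:
- any cancer: (0.65/0.35) / (0.55/0.45) = 1.52;
- score 7 or more: (0.38/0.62) / (0.35/0.65) = 1.14;
- score 8: (0.16/0.84) / (0.15/0.85) = 1.08.

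These are far from common. A single odds ratio would be driven mainly by extra score-6 cancers, and Introduction and rationale counts detection of cancers that are not clinically relevant among the problems to be solved.

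**The case against.** The article nowhere says that men with benign biopsies are left out. It offers ordinal regression as well as linear, under an intention-to-treat rule, and an ordinal outcome with no cancer as the lowest level on all randomised men would fit the text. Coding of benign biopsies is the kind of detail that an unseen analysis plan may settle. That much stands: a reader might infer that the plan expressly excludes these men and so contradicts itself outright, and the wording does not support that. It does not rescue the linear option, which is a stated method and cannot include a benign biopsy without an arbitrary score.

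The question that matters is also already answered on all randomised men, through the counts of cancers and of clinically significant cancers per group. Gleason Score is in neither the outcome list under Objectives nor the secondary list under Objective 2; it appears only as an example in a modelling sentence. This stands too and limits the point to a supporting analysis.

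Finally, the size is assumed and can be small. In the example of step 5, the mean falls from 6.91 to 6.83 with 132 and 156 men. With an SD of about 0.79 the standard error is about 0.094, so z is about 0.8 and p about 0.4. This is fair: the harm is a misdirected comparison, not necessarily a significant one.

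**Conclusion.** The point holds for the Gleason Score regression. Run as linear regression, or as ordinal regression on cancers only, it compares subsets selected after randomisation by the outcome under test, and it does not follow the stated intention-to-treat principle. The direction can go either way. Under the assumed detection rates and grade mixes, the spurious mean difference runs from −0.20 to +0.15, on 96–120 vs 108–156 men instead of 240 vs 240. These figures hold the grade of TRUS-detectable cancers fixed; none of the rates comes from the document.

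Three further inferences are not supported:
- That the secondary objective is compromised. The counts of cancers and clinically significant cancers per randomised group do not condition on detection.
- That number of lesions, named in the same sentence, fails in the same way. A benign biopsy can count as 0.
- That fusion biopsy will look worse. That happens only if the extra cancers are of lower grade.

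The change should be made, but the key randomised results do not depend on it.

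**What to change.** 1. Delete linear regression as an option for Gleason Score.
2. Base the between-arm inference on grade on clinically significant cancer (yes/no), by the trial's own definition, with every randomised man in the denominator and the planned covariates.
3. If an ordinal model is kept, fit it to all randomised men with no cancer on biopsy as the lowest level. Report the odds ratio at each threshold and do not rely on one proportional-odds estimate.
4. Report Gleason Score among cancer-positive men by arm as descriptive only, without a test.

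The cost is a few lines of wording and a little extra analysis. No new data are needed. The change should be fixed before the arms are compared.
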